## Abstract

**Background/aims:**

Despite evidence that preferential use of balanced/buffered fluids may improve outcomes compared with chloride-rich 0.9% saline, saline remains the most commonly used fluid for children with septic shock. We aim to determine if resuscitation with balanced/buffered fluids as part of usual care will improve outcomes, in part through reduced kidney injury and without an increase in adverse effects, compared to 0.9% saline for children with septic shock.

**Methods:**

The Pragmatic Pediatric Trial of Balanced versus Normal Saline Fluid in Sepsis (PRoMPT BOLUS) study is an international, open-label pragmatic interventional trial being conducted at > 40 sites in the USA, Canada, and Australia/New Zealand starting on August 25, 2020, and continuing for 5 years. Children > 6 months to < 18 years treated for suspected septic shock with abnormal perfusion in an emergency department will be randomized to receive either balanced/buffered crystalloids (intervention) or 0.9% saline (control) for initial resuscitation and maintenance fluids for up to 48 h. Eligible patients are enrolled and randomized using serially numbered, opaque envelopes concurrent with clinical care. Given the life-threatening nature of septic shock and narrow therapeutic window to start fluid resuscitation, patients may be enrolled under “exception from informed consent” in the USA or “deferred consent” in Canada and Australia/New Zealand. Other than fluid type, all decisions about timing, volume, and rate of fluid administration remain at the discretion of the treating clinicians. For pragmatic reasons, clinicians will not be blinded to study fluid type. Anticipated enrollment is 8800 patients. The primary outcome will be major adverse kidney events within 30 days (MAKE30), a composite of death, renal replacement therapy, and persistent kidney dysfunction. Additional effectiveness, safety, and biologic outcomes will also be analyzed.

**Discussion:**

PRoMPT BOLUS will provide high-quality evidence for the comparative effectiveness of buffered/balanced crystalloids versus 0.9% saline for the initial fluid management of children with suspected septic shock in emergency settings.

**Trial registration:**

PRoMPT BOLUS was first registered at ClinicalTrials.gov (NCT04102371) on September 25, 2019. Enrollment started on August 25, 2020.

**Supplementary Information:**

The online version contains supplementary material available at 10.1186/s13063-021-05717-4.

## Background

Crystalloid fluid is part of the initial resuscitation for 25 million children with septic shock worldwide each year [1]. Options for crystalloid resuscitation include 0.9% saline or balanced/buffered fluids (lactated Ringer’s [LR], Hartmann’s solution, PlasmaLyte). Saline contains a supra-physiologic concentration of chloride and low strong ion difference (SID) that induce hyperchloremic metabolic acidosis, decrease renal blood flow, and promote inflammation [2, 3]. In contrast, balanced/buffered fluids have less chloride, some additional electrolytes, and a higher SID due to an anion buffer. Balanced/buffered fluids have been associated with better outcomes compared to 0.9% saline, including decreased acute kidney injury (AKI), need for renal replacement therapies (RRT), and death in adult [4–10] and pediatric [11] studies, while others reported no benefit [12] or harm [13]. Notably, 0.9% saline remains the most commonly used fluid for children with septic shock due to historical preference, universal availability, ease of use, drug compatibility, lower cost, and lack of definite benefit for alternatives [14–16].

The Isotonic Solutions and Major Adverse Renal Events Trial (SMART) found a small, but significant, reduction in major adverse kidney events within 30 days (MAKE30) with the use of balanced/buffered fluids compared to 0.9% saline in critically ill adults [17]. The largest benefits were in sepsis, with 4.2% lower mortality for balanced/buffered fluids. A parallel trial found similar benefits in non-critically ill adults [18]. In children, however, the two largest studies of fluid type in sepsis are observational and reached opposing conclusions [19, 20]. Consequently, recent guidelines issued a weak suggestion for balanced/buffered crystalloids while calling for studies to compare the effectiveness of different fluid types in pediatric septic shock [21, 22].

The primary aim of the Pragmatic Pediatric Trial of Balanced versus Normal Saline Fluid in Sepsis (PRoMPT BOLUS) is to determine if resuscitation with balanced/buffered fluids as part of usual care will improve outcomes compared to 0.9% saline for children with septic shock. Secondary aims are to compare the relative safety and determine the differential effect of each fluid type on kidney injury biomarkers in children with septic shock. We hypothesize that balanced/buffered fluid resuscitation will reduce MAKE30 (a composite of death, new RRT, or persistent kidney dysfunction) compared to 0.9% saline, in part through reduced kidney injury, without an increase in adverse effects. Notably, even a small clinical benefit would be important because sepsis is common, life-threatening, and the proposed practice change is inexpensive and readily available.

## Methods

This manuscript was written in accordance with Standard Protocol Items: Recommendations for Interventional Trials (SPIRIT) guidelines (Additional file 1) and the 2010 CONSORT recommendations for pragmatic trials [23].

### Trial design

PRoMPT BOLUS is a multicenter, open-label, pragmatic interventional trial in which children with suspected septic shock are randomized to receive either 0.9% saline or balanced/buffered crystalloid fluids for initial resuscitation and maintenance fluids in addition to usual care. A pragmatic design [24] was selected to optimize cost-efficiency and generalizability (Table 1), and in a pilot study, was demonstrated to be feasible to implement within a busy pediatric emergency department [25]. Figure 1 shows an overview of the study design and Fig. 2 is the SPIRIT summary of study activities.

**Table 1 Tab1:** Key features of explanatory versus pragmatic clinical trials^a^

Study element	Explanatory clinical trial	Pragmatic clinical trial	Considerations for PRoMPT BOLUS
Objective	Mechanism or efficacy	Effectiveness	Comparative effectiveness of two existing standards of care
Study population	Restrictive, homogeneous (“ideal” target population)	Heterogeneous (“real-world” clinical practice)	Children treated with fluid therapy for suspected septic shock with abnormal perfusion as per treating clinician judgment
Intervention	Inflexible, strictly enforced	Usual practice #1	Balanced/buffered crystalloid fluid (site/clinician preference to use lactated Ringer’s, PlasmaLyte, or Hartmann’s)
Comparison	Inflexible, placebo, or usual practice	Usual practice #2	0.9% saline
Data collection	Extensive, labor-intensive	Targeted, limited	Targeted and limited to essential data to ensure balance in key covariates between study groups and to collect all outcomes
Protocol implementation and oversight	Dedicated study team assists with enrollment and study procedures	Treating clinicians carry out study procures embedded within clinical practice	Emergency physicians will be trained to screen, enroll, randomize, and initiate study fluids for bolus and maintenance therapy
Protocol adherence	Closely monitored with tight parameters	Unobtrusive or none	Guidance provided to treating clinicians to use randomized study fluid for bolus and maintenance fluid therapy from randomization through 11:59 PM of the following calendar day; non-study fluids allowed for specific clinical indications at clinicians’ judgment. Final adherence defined as receipt of ≥75% of total crystalloid administered by type assigned in the intervention phase.
Outcome(s)	Specialized experts often involved in quantifying study endpoints that are direct consequence of intervention	Endpoints are objective, clinically meaningful, and easily measured as part of routine clinical practice	MAKE30, mortality, hospital-free days, adverse events, and biomarkers all defined with objective criteria; effectiveness and safety outcomes all patient-centered.
Analysis	Intention-to treat with interpretation that intervention improves outcomes under “ideal” conditions	Intention-to-treat with interpretation that intervention improves outcomes under “usual” conditions	Intention-to-treat analysis will be interpreted as the comparative effectiveness between predominant—rather than exclusive—use of balanced/buffered fluids versus 0.9% saline
Generalizability	Variable (though often low)	Variable (though typically high)	Expected to be highly generalizable
Costs	Relatively high	Relatively low	Relatively low for large clinical trial

^a^Adapted from Thorpe et al *Journal of Clinical Epidemiology* 2009

**Fig. 1 Fig1:**
[figure not shown]
Schematic overview of the study design

**Fig. 2 Fig2:**
[figure not shown]
SPIRIT summary of study activities

### Participants

All patients > 6 months to < 18 years treated for suspected septic shock with parenteral antibiotics and at least one fluid bolus for abnormal perfusion in a study site ED will be eligible for study enrollment. The lower age was selected to adhere to the US Food and Drug Administration (FDA) warning that infants < 6 months may have reduced hepatic capacity to metabolize exogenous lactate in LR. “Suspected septic shock” is operationalized as a) the treating clinician’s diagnosis of septic shock and/or treatment that includes parenteral antibiotic and fluid resuscitation for abnormal perfusion or b) a sepsis alert on a site-specific screening tool with clinician confirmation to proceed with treatment for suspected septic shock. Abnormal perfusion is defined as the treating clinician’s judgment that hypotension or abnormal (either “flash” or “prolonged”) capillary refill is present. To reflect usual clinical practice, we do not define thresholds for hypotension or abnormal capillary refill but rather defer to the treating clinician’s discretion to differentiate abnormal from normal. Recognizing that fluid resuscitation may start prior to ED arrival, only those for whom total volume of crystalloid fluid administration can be confirmed as ≤40 mL/kg will be eligible.

Exclusion criteria are (1) clinician judgment that the patient’s condition deems it unsafe to administer either 0.9% saline or balanced/buffered fluids (see Additional file 2), (2) known pregnancy at time of assessment for eligibility, (3) known prisoner at time of assessment for eligibility (in USA, Australia/New Zealand), (4) patient is a ward of the state (in Australia/New Zealand), (5) known allergy to either fluid type, or (6) prior indication that patient would not agree to be enrolled in the study.

### Research ethics approval

A single Institutional Review Board at The Children’s Hospital of Philadelphia (CHOP) will provide regulatory approval and oversight for all US study sites. In Canada, the University of Calgary will sponsor regulatory approval through Health Canada, while each site’s Research Ethics Board will oversee local human subjects’ protections (except sites in Ontario, for which centralized approval through Clinical Trials Ontario will be obtained). In Australia and New Zealand, a single ethics committee will provide regulatory oversight within each jurisdiction. Protocol modifications approved by the international steering committee will be first reviewed by the CHOP Institutional Review Board and, following approval, will be distributed by the network-specific principal investigators to all other regulatory bodies in the USA (local site Institutional Review Boards, FDA), Canada, Australia, and New Zealand, as well as to local investigators.

### Consent

Prospective written informed consent will be sought from a legally authorized representative (LAR, e.g., at least one parent) prior to enrollment *when sufficient time permits*. However, because of the life-threatening nature of septic shock and narrow therapeutic window to commence fluid resuscitation, enrollment may proceed in the USA under the federal “Exception From Informed Consent” (EFIC, 21 CFR 50.24) for emergency research [26] and in Canada and Australia/New Zealand with “deferred consent” in compliance with the Canadian Tri-Council Policy Statement-2 [27] and National Statement on Ethical Conduct in Human Research [28], respectively. Such enrollment methods are ethically suitable for emergent, life-threatening conditions when patients may benefit from the research, available treatments are unproven/unsatisfactory, and obtaining prospective informed consent is not feasible [25, 29–32]. A waiver of assent will be requested due to the critical nature of illness in septic shock.

To comply with federal and ethical guidelines, community consultation and public disclosure were conducted in the USA (available at https://www.regulations.gov/docket/FDA-1995-S-0036) and community consultation was conducted in Australia/New Zealand to obtain input from and inform the local community prior to beginning enrollment [33, 34]. All EFIC studies are also subject to additional regulation through the US FDA, which approved the study protocol under an Investigational New Drug (IND #136978) application.

Participants enrolled under EFIC (USA) or deferred consent (Canada, Australia/New Zealand) will be notified of enrollment and study procedures as soon as feasible and offered the right to withdraw from or continue in the study. For study participants who die prior to the post-enrollment discussion in the USA or deferred consent in Canada or Australia/New Zealand, all reasonable attempts will be made to inform the LAR after the participant’s death, unless a waiver has been granted in local jurisdictions. However, successful LAR contact will not be required to include data in the analysis. At a subset of sites collecting biological samples, separate written informed consent will be obtained for the measurement of blood and urine biomarkers.

### Intervention

The intervention to be tested is predominant fluid resuscitation with balanced/buffered fluids (LR, Hartmann’s, or PlasmaLyte, as per local site preference) compared to the “usual practice” of predominant 0.9% saline resuscitation. Other than prescribing which crystalloid fluid type to use, the intervention will be implemented without efforts to standardize timing and volume of fluid resuscitation or other components of clinical care. Thus, all decisions to administer fluid, as well as timing, volume, and rate of fluid administration, remain at the discretion of the treating clinicians. Hospital fluid supplies will be used for this study without any change to packaging or labeling. Participants will be randomized to receive either balanced/buffered fluids or 0.9% saline for all bolus and maintenance fluid administration starting from randomization through 11:59 pm on the following calendar day. Maintenance fluids are included because these constitute a substantial proportion of total crystalloid fluid administration [35], including 40% of total crystalloids as maintenance fluids in our pilot study [25]. If the treating clinician deems it unsafe to continue study fluid or identifies a clinical indication that requires specific fluid or electrolyte therapy (e.g., hyponatremia, hyperkalemia, hypercalcemia, cerebral edema), non-study fluids are permitted. Use of non-isotonic fluids (e.g., 0.45% saline) is not recommended as standard maintenance fluids in children [36] and will be discouraged during the intervention phase. Colloid fluids and blood products may be administered at the discretion of the treating team.

Ending the intervention phase at 11:59 PM on the calendar day following randomization ensures all participants are eligible to receive study fluid for a minimum of 24 and a maximum of 48 h. This represents the time-window from the presentation during which most fluid resuscitation is completed for septic shock [17] and provides a pragmatic endpoint that signals the end of the intervention phase.

### Adherence

All fluid administered through the end of the intervention window will be recorded. Adherence to the intervention is defined as receipt of ≥75% of total crystalloid fluid as the randomized fluid type during the interventional window. For example, participants randomized to balanced/buffered fluids are considered adherent to the intervention if they receive ≥75% of their total crystalloid as balanced/buffered fluids starting from the time of randomization through 11:59 PM on the following calendar day. Locally, all sites will establish a work-flow to communicate study enrollment and promote adherence across providers and hospital locations. Such strategies include verbal and/or written hand-offs between providers, use of a templated orderset indicating PRoMPT BOLUS study enrollment and treatment allocation, and automated electronic reminders to clinicians at the time an order is placed for non-study crystalloid fluids during the intervention window. Each participant’s adherence to the intervention will be monitored centrally, and the mean adherence to the intervention for all participants within each site will be regularly reported back to local investigators. Targeted education will be undertaken if < 80% of participants in either study arm meet the adherence criterion. If < 70% of participants meet the adherence criterion over two consecutive months, the site will be placed on monitored probation with additional efforts undertaken to understand and correct challenges to adherence. Sites that continue to fail to meet the adherence threshold in at least 80% of enrolled participants may be removed from study participation.

### Data collection and management

Data will be extracted from the medical record and recorded onto a standardized case report form. Each network will oversee data collection and quality from its respective sites. In the USA, data will be collected through FDA-compliant Advarra Electronic Data Capture (Columbia, MD) hosted at CHOP. In Canada and Australia/New Zealand, data will be collected in Research Electronic Data Capture (REDCap, Vanderbilt University; Nashville, TN) hosted at the University of Alberta and the Murdoch Children’s Research Institute, respectively [37]. However, all sites will collect the same data elements using a common data dictionary. All study data will be password-protected and coded with a study number to ensure confidentiality. Periodic verification of study data against source documents will be undertaken within each network to certify data accuracy. The US Data Coordinating Center (DCC) will centrally manage all data exported from Advarra and REDCap to ensure harmonization for analyses. Consistent with the tenets of a pragmatic trial, data collection will be brief, targeting key patient characteristics, fluid administration, and outcomes (Additional file 3).

### Outcomes

The primary outcome will be MAKE30—a composite of death from any cause, initiation of RRT, or persistent kidney dysfunction—at either 30 days following study enrollment or hospital discharge, whichever comes first (Table 2) [38]. RRT will include treatment (or attempt to treat if the participant does not tolerate treatment) with any renal replacement modality during the hospitalization that was not a continuation of pre-hospital chronic therapy, censored at 30 days after randomization. Persistent kidney dysfunction will be measured as final creatinine ≥200% of baseline (i.e., at least a doubling of baseline creatinine) *and* a minimum absolute increase of ≥0.3 mg/dL. Baseline serum creatinine will be recorded as the lowest creatinine available between 12 months and 24 h prior to enrollment or, for participants without such data, an imputed value using established median values for age and sex [39]. Secondary efficacy, safety, and biologic outcomes are listed in Table 2.

**Table 2 Tab2:** Study outcomes

Outcome	Definition
Primary outcome	
MAKE30 (primary outcome)	Major adverse kidney events at 30 days (defined as at least one of the following): • Death • New renal replacement therapy • Persistent kidney dysfunction at hospital discharge or 30 days (serum creatinine ≥2x baseline or median value for age if no baseline available *and* a minimum absolute increase of ≥0.3 mg/dL)
Secondary effectiveness outcomes	
Death	All-cause mortality at hospital discharge, 28 days, and 90 days^b^
Hospital length of stay	Days from hospital admission until discharge, censored at 90 days
Hospital-free days out of 28 days	Days between enrollment and day 28 in which patient was alive and out of the hospital
New inpatient renal replacement therapy	New continuous renal replacement therapy, hemodialysis, or peritoneal dialysis
Persistent kidney dysfunction at hospital discharge	Serum creatinine ≥2x baseline or median value for age if no baseline^a^ available, censored at 30 days
Secondary safety outcomes^c^	
Hyperlactatemia	> 4 mMol/L
Hyperkalemia	> 6 mEq/L
Hypercalcemia	Ionized calcium > 1.35 mmol/L or total serum calcium > 12 mg/dL
Hypernatremia	> 155 mEq/L
Hyponatremia	< 128 mEq/L
Hyperchloremia	> 110 mEq/L
Thrombosis	Therapy for new arterial or venous thrombus with systemic anticoagulant OR Clotting of intravenous catheter in subjects receiving ceftriaxone and lactated Ringer’s
Cerebral edema	Therapy with hyperosmolar therapy (hypertonic saline and/or mannitol) for radiographic and clinical determination of new impending or present brain herniation
Secondary biologic outcomes^d^	
Urine neutrophil gelatinase-associated lipocalin	Biomarkers will be measured on the day of randomization (day 0), day 2, and day 27 (or prior to death or anticipated discharge, whichever comes first). Analyses will include between-group differences in absolute biomarker values at each timepoint and, to account for potential baseline differences, the percent change in biomarkers relative to measurements on study 0.
Urine kidney injury molecular-1	
Urine liver-type fatty acid-binding protein	
Urine interleukin-18	
Plasma cystatin C	

^a^Baseline creatinine will be determined for each study participant as the lowest recorded creatinine available between 12 months and 24 h prior to the index admission. For participants without such data available, an estimated baseline creatinine will be imputed using previously established median values for age and sex

^b^Mortality at 90 days will be measured using vital status obtained from the medical record at all sites, as well as the US National Death Index and Canadian provincial vital statistics if vital status cannot be confirmed using medical records alone

^c^Safety outcomes must occur within 4 calendar days of randomization, except thrombosis which must occur within 7 days of randomization

^d^Plasma and urine biomarkers of kidney injury will also be collected from study participants enrolled at a subset of sites

The rationale for MAKE30 as the primary endpoint is that mediation of kidney injury provides the major mechanistic pathway through which balanced/buffered fluids are likely to improve patient outcomes. In addition, the only prior comparable randomized clinical trials demonstrated a reduction in MAKE30 with the use of balanced/buffered fluids in adult patients with sepsis [17, 18]. Finally, MAKE30 provides an objective and easily measured outcome endorsed as a patient-centered endpoint for clinical trials [40].

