**Fig. 3 Fig3:**
[figure not shown]
Flow diagram of patients progressing through the trial

**Table 3 Tab3:** Patient characteristics

Characteristic	0.9% saline	Balanced/buffered fluid
	(*n* = )	(*n* = )
Country of enrollment, *n* (%)		
USA		
Canada		
Australia/New Zealand		
Age in years, median (IQR)		
Age category, *n* (%)		
6 mos to < 1 year		
1 year to < 5 years		
5 years to < 12 years		
12 years to < 18 years		
Sex, *n* (%)		
Male		
Female		
Other/unknown		
Race, *n* (%)		
White		
Black		
Asian		
American Indian/Alaska Native		
Native Hawaiian/Other Pacific Islander		
Unknown/not reported^a^		
Ethnicity, *n* (%)		
Hispanic or Latino		
Aboriginal or Torres Strait Islander		
Maori		
Other^b^		
Unknown/not reported^a^		
Weight (kg), median (IQR)		
Comorbid conditions, *n* (%)		
Cancer (hematogenous or solid tumor)		
Bone marrow or solid organ transplant		
Cardiomyopathy or heart failure		
Pulmonary hypertension		
Kidney disease (not on dialysis)		
Neurologic dysfunction causing severe developmental delay		
Sickle cell disease		
Chronic ventilator dependence		
Indwelling central line		
Site of infection, *n* (%)		
Primary bloodstream		
Pneumonia or other lung infections		
Abdominal		
Genitourinary		
Central nervous system		
Skin/soft tissue		
Other infection		
Unknown site		
Alternative diagnosis (not infection)		
Positive blood culture (bacteremia) as either primary or additional site of infection, *n* (%)		
Concurrent Therapies (through study day 1, 11:59 pm)		
Antibiotics prior to study site ED arrival, *n* (%)		
Minutes to first antibiotic administration after ED arrival, median (IQR)^c^		
Ceftriaxone, *n* (%)		
Vasoactives, *n* (%)		
Corticosteroids, *n* (%)		
Bicarbonate or other buffers, *n* (%)		
Invasive mechanical ventilation^d^, *n* (%)		
Extracorporeal membrane oxygenation, n (%)		
Baseline creatinine (mg/dL)^e^, median (IQR)		
KDIGO acute kidney injury stage at enrollment, *n* (%)		
Stage 1		
Stage 2		
Stage 3		

*KDIGO*, Kidney Disease: Improving Global Outcomes

^a^Race and ethnicity not available from participants enrolled in Canadian sites

^b^“Other” ethnicity includes participants who identified as not Hispanic or Latino in the USA and not Aboriginal or Torres Strait Islander or Maori in Australia/New Zealand

^c^Includes only the subset of participants (*n* = ) who did not receive antibiotics prior to study site ED arrival

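### The MAKE30 definition sets aside chronic dialysis in its RRT component but not in its creatinine component, so some children already on chronic RRT can be scored as false primary events

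*Protocol article*

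**What the plan says.** All of the following is in the protocol article.

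- **RRT component (Outcomes).** It counts RRT of any kind given in hospital "that was not a continuation of pre-hospital chronic therapy". This qualifier has work to do only if children already on chronic RRT can be in the trial.
- **Creatinine component (Outcomes).** "Persistent kidney dysfunction will be measured as final creatinine ≥200% of baseline (i.e., at least a doubling of baseline creatinine", together with a minimum absolute rise of 0.3 mg/dL. Table 2 gives the same rule as "serum creatinine ≥2x baseline or median value for age if no baseline available". Neither place mentions chronic RRT.
- **Baseline (Outcomes; Table 2, note a).** "Baseline serum creatinine will be recorded as the lowest creatinine available between 12 months and 24 h prior to enrollment", or failing that "an imputed value using established median values for age and sex". Note a gives this rule the widest scope: "Baseline creatinine will be determined for each study participant as the lowest recorded creatinine available between 12 months and 24 h prior".
- **Composite (Table 2).** Any one component makes a primary event.
- **Eligibility (Participants).** None of the six exclusions names dialysis or end-stage kidney disease. The first rests on clinician judgment that either fluid would be unsafe and refers to Additional file 2.
- **Baseline table (Table 3).** The comorbidity row reads "Kidney disease (not on dialysis", and there is no row for children on dialysis.
- **Primary analysis (Statistical analysis).** Intention to treat, in all randomized children for whom none of the three components is missing.

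**The concern.** The RRT component is written so that a child who arrives on chronic dialysis and stays on it is not counted as having a new kidney event. The creatinine component, as printed, can count the same child by another route.

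- **Measured baseline.** The rule takes the lowest value over a year. In a child on dialysis that minimum may be a post-dialysis trough. The value it is compared with is whichever creatinine was last. A later pre-dialysis value can be double the trough, and more than 0.3 mg/dL above it, without any new injury.
- **Imputed baseline.** If no earlier value is on file, the comparator is a population median for age and sex. A dialysis-level creatinine would very likely exceed twice that.

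Such an event does not measure the kidney injury that the article gives as its reason for choosing MAKE30. It is also unrelated to fluid type, so it pulls the relative risk towards 1. The Sample size section chose 95% power on purpose because the expected absolute difference is small, and avoidable dilution works against that choice.

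**Working it through.** **Inputs from the article.** 8800 children, 1:1, so 4400 per arm; MAKE30 6.0% on saline and 4.3% on balanced fluid; type I error 0.05 in the sample-size statement (taken as two-sided) and 0.044 at the final analysis.

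**Inputs that are assumed.** The share f of enrolled children on chronic RRT (0.25% to 1%) and the chance q that such a child is falsely flagged (50%). The article gives neither.

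**Step 1. Reproduce the plan's figure.** Power = Φ[(d − z·SE0)/SE1], where SE0 uses the pooled proportion and SE1 the separate proportions.
- d = 0.060 − 0.043 = 0.017; pooled proportion 0.0515.
- SE0 = √(0.0515 × 0.9485 × 2/4400) = 0.00471.
- SE1 = √[(0.06 × 0.94 + 0.043 × 0.957)/4400] = 0.00471.
- At 0.05: (0.017 − 1.960 × 0.004712)/0.004709 = 1.649, power 95.0%. The stated 95% reproduces.
- At 0.044: (0.017 − 2.014 × 0.004712)/0.004709 = 1.595, power 94.5%. This is the reference for what follows.
- Planned relative risk 0.043/0.060 = 0.717. Planned events 4400 × (0.060 + 0.043) ≈ 453.

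**Step 2. Add false events equally to both arms.** With s = f × q, the risks become 0.060 + s and 0.043 + s, and the number of false events is 8800 × s.

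| f | q | s | False events | Risks | Relative risk | Power at 0.044 |
|---|---|---|---|---|---|---|
| 0 | – | 0 | 0 | 6.00% v 4.30% | 0.717 | 94.5% |
| 0.25% | 50% | 0.00125 | 11 | 6.125% v 4.425% | 0.722 | 94.0% |
| 0.5% | 50% | 0.0025 | 22 | 6.25% v 4.55% | 0.728 | 93.5% |
| 1% | 50% | 0.005 | 44 | 6.50% v 4.80% | 0.738 | 92.5% |

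**Step 3. Allow for overlap.** Some flagged children would be events anyway, for example through death. If they otherwise carry the planned risks, the new risks are 0.060 + 0.940s and 0.043 + 0.957s. At s = 0.005 these are 6.47% and 4.78%, with relative risk 0.739 and power 92.4%. At s = 0.00125 power is still 94.0%. Overlap makes no practical difference.

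**The case against.** The strongest reply is that the article condenses a fuller protocol. Additional file 2 expands the clinician-judgment exclusion and is not shown, and it may keep some of these children out. The Table 3 row shows that the authors had dialysis patients in mind, so special handling may be set out elsewhere. This limits confidence in the size of the problem. It does not remove the asymmetry: the primary outcome is defined explicitly, chronic therapy is dealt with in one component only, and the baseline rule is stated to cover every participant.

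The size is also open to challenge, and fairly.

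- **The inputs are assumed.** Both the share of children and the flag rate lack any source in the article.
- **The planning rates may already contain such events.** The 6% was set from observed MAKE30 rates of 5.0% to 9.7%. If those populations included dialysis patients scored in the same way, adding false events on top counts them twice and the true loss is smaller.

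A reader might infer more than the text supports:

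- **That a child with an imputed baseline is an event by definition.** The final creatinine must still reach twice the median and rise by at least 0.3 mg/dL. That is very likely at dialysis levels but not automatic. The route should also be uncommon, since children on dialysis can be expected to have a creatinine on file from the past year (an assumption).
- **That nearly all such children would be flagged.** If the imputed route is uncommon, most flags depend on the trough route, and the article gives no frequency for that.
- **That the comparison is biased towards one fluid.** Allocation is 1:1 within site, so false events are expected equally in both arms.

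**Conclusion.** The point holds as a minor flaw in the primary outcome definition. Followed as printed, the creatinine component can turn a dialysis-related swing, or the gap between a dialysis-level value and a normal median, into a MAKE30 event, although the RRT component excludes the same child's continuing therapy. The expected consequence is dilution without direction.

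The size is unknown. Under the assumed 0.25-1% on chronic RRT with half flagged, the loss is about 0.5 to 2 percentage points of power at 0.044. It is less if the planning rates already include such events, and nil if an unseen file excludes or exempts these children. Power stays above 92% throughout this range, so the trial's ability to answer its question is not in doubt. The case for acting is that the outcome should mean the same thing in all its components and that the correction is cheap.

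**What to change.** Add to the outcome definition that participants receiving chronic RRT before enrolment are coded as no event on the new-RRT and creatinine components, remain in the intention-to-treat set, and can meet MAKE30 only through death. The coding must say no event and not merely inapplicable. The primary analysis keeps only children with no component missing, so an inapplicable component could be read as missing and drop them.

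Apply the same clause to the secondary outcome of persistent kidney dysfunction, add a row to Table 3 giving the number of such children by arm, and specify a sensitivity analysis of MAKE30 that excludes them. If Additional file 2 or the full protocol already excludes or exempts them, a cross-reference is enough.

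**Cost.** No new data should be needed, because chronic-RRT status must already be known to score the RRT component. Randomization and sample size do not change. These few children would contribute only deaths. Because enrolment is under way in an open-label trial, the change to the primary outcome needs a short dated amendment.
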